### **Part C: Multiple dose part with the niclosamide solution**

The multiple dose part (Part C) will start in parallel to Part B since Part B will only be performed to get information about the relative bioavailability of the niclosamide solution compared to the approved niclosamide chewing tablets. The chosen dose of the niclosamide solution in Part B is identical with the highest dose given under fed conditions in Part A of this study, which was safe and well tolerated. Thus, there is no additional risk to start with Part C in parallel to Part B.

Part C is comprised of a screening visit (between Day -21 and Day -2), a baseline evaluation (Day -1), a multiple dose treatment period (Day 1 through Day 7, discharge on Day 8) with OD dosing of niclosamide solution and one EOS visit between Day 10 and Day 12.

Part C consists of three parallel groups:

Group 1: 1200 mg niclosamide solution (n=4)

Group 2: 1600 mg niclosamide solution (n=4)

Group 3: Placebo (n=4)

The high dose of niclosamide solution can be stopped and continue with the medium dose in the subsequent subjects, if moderate to severe GI side effects occur most likely due to an accumulation of the excipient PEG-400 in the gut.

Approximately 12 subjects (4/group) will be enrolled in this part of the study, who receive the niclosamide solution (1200 mg and 1600 mg QD) or placebo over a treatment period of 7 days. The dose of the niclosamide solution depends on the safety and PK results of Part A and will not exceed 1600 mg QD.

Subjects will remain domiciled in the study site from Day -1 until the Day 8 (24h post dose) and until all assessments have been completed. Subjects will be allowed to leave the study center on Day 8 at the discretion of the Investigator, if there are no prohibitive safety findings. The subjects will be asked to return to the study site for the EOS assessments on Day 10 (+2 days). The EOS evaluation has also to be performed if a subject prematurely terminates the study for any reason.

All baseline safety evaluations results must be available prior to dosing.

#### **3.1.1. Replacements**

Drop-outs will be replaced to obtain 4 completed subjects at the end of dose levels in Part A and to complete the planned subjects in Part B and Part C. Replacements will receive the same treatments as the drop outs.

## **3.2. Rationale for Study Design**

A niclosamide solution has been developed that is expected to release the drug substance more readily and more reproducibly.

This 3-part study is designed to investigate (1) safety and pharmacokinetics of single ascending doses of the new niclosamide solution formulation after fasted and fed conditions, (2) the relative bioavailability of the new solution compared to the chewing tablet, and (3) safety and pharmacokinetics of multiple doses of the niclosamide solution in healthy volunteers.

[figure not shown]

Healthy volunteers: Healthy volunteers have been selected for this 3-part study to reduce the variability in the pharmacokinetics of niclosamide due to interfering factors such as drug-drug interactions with concomitant medications and underlying diseases. The findings in this population are expected to adequately predict findings in the target patient population for which the niclosamide solution is intended, i.e. COVID-19 infected patients.

SAD design (Part A): Sequentially increasing the oral solution dose from one cohort to the next allows the SMC and the investigator to get key data from the preceding cohorts prior to making a decision whether the next cohort is safe to be exposed to a higher oral solution dose.

Sentinel dosing (Part A): By initially dosing one subject of niclosamide solution in each cohort prior to dosing of the remaining subjects controls the risk of potentially high-frequency serious or severe adverse events which are acute and monitorable, such as gastrointestinal disorders. Due to the expected short half-life of niclosamide, safety signals are expected to occur within 24 h after the drug administration. Sentinel dosing will be implemented in the SAD cohorts to minimize the risk for the remainder of the cohorts. The treatment stopping rules, cohort stopping rules and study stopping rules will guide decisions on administering next doses to subjects.

Crossover (Part B): The two-sequence, two-period crossover design is considered appropriate to minimize variability of PK parameters. A washout-period of only 2 days reflect the short half-life of 2 to 5 hours of the niclosamide chewing tablet, but will be extended, if the half-life of the niclosamide solution formulation (determined in Part A) turns out to be longer. The washout-period will cover at least 5 half-lives based on the PK results in Part A.

Placebo-control: A placebo control is included in cohorts A and C that may allow to differentiate between drug-related AEs and AEs which might occur in the absence of active treatment.

Food effect: The last cohort in Part A will be repeated under fed conditions. It is expected that food influences the systemic exposure of niclosamide solution formulation.

MD design of Part C: A MD design was chosen to obtain safety and PK data over a treatment period which is comparable with the treatment period in COVID-2 infected patients.

### **3.3. Stopping Rules for Dose Escalation (Part A)**

#### **Safety stopping rules**

Safety data of all subjects in a given cohort until Day 2 must be reviewed. If one or more of the following criteria is met, dosing will be paused at any time during the study and the SMC will be consulted.

- Occurrence of a serious adverse event (SAE) assessed as related to the IMP in at least one subject.
- Occurrence of severe (Grade  $\geq 3$  based on common terminology criteria for adverse events [CTCAE]) adverse events (AE) assessed as related to IMP in two subjects in the same cohort, independent of within or not within the same system-organ-class.
- Occurrence of relevant (as judged by the investigator) and confirmed safety lab deviations in two or more subjects.

The study may continue after comprehensive review by the SMC if the safety signals obtained are considered not to preclude further dosing within the cohort. Dose escalation of the niclosamide solution will only be performed if the SMC and the Investigator confirm and agree that the current emerging safety and tolerability data support dose escalation.

[figure not shown]

### **Stopping Rules for dose escalation based on PK data**

Dose escalation to the next higher cohort will be stopped if the plasma levels of the niclosamide solution is above 5 µM (approx. 1.6 µg/ml) at 8h post-dosing in all subjects treated with niclosamide. It is noted that this limit is not informed by safety concerns but by efficacy considerations. 5 µM trough is estimated to be in a sufficiently therapeutic range.

### **3.4. Stopping Rules for the 1600 mg Dose Group (Part C)**

The dosing of the high dose group (1600 mg) may be discontinued if moderate to severe GI side effects occur which are most likely due to accumulation of the excipient PEG-400 in the gut.

In that case, the SMC will review the safety data. Subsequent subjects in the high dose group will receive the medium dose of 1200 mg if the SMC and the Investigator confirm and agree that the safety data support this decision.

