|                                    | 
*Part B will only be initiated after approval from Ethics Committee and Competent Authority via a substantial amendment, along with the relevant PK, and safety data from the niclosamide solution from Part A.
 
Part C is a randomized, double-blinded, placebo-controlled multiple dose study investigating the safety and PK of the niclosamide solution over a treatment period of 7 days. This part consists of three treatment groups, which will start in parallel: Group 1 1200 mg (n=4), Group 2 1600 mg (n=4) and group 3 placebo (n=4). The 1600 mg niclosamide dose will be stopped and continued with the 1200 mg dose if the 1600 mg dose causes intolerable side effect, most likely GI side effects due to the amount of PEG-400 in the new formulation.
 
In total, 12 subjects will be enrolled in this part of the study.
 
Part B and Part C will start in parallel, since Part B will only be performed to get information about the relative bioavailability compared to the approved chewing tablets. The chosen dose of the niclosamide solution in Part B is identical with the highest dose given in Part A of the study which was safe and well tolerated. Thus, there is no additional risk to start with Part C in parallel to Part B.
 
A Safety Monitoring Committee (SMC) will continuously monitor subject safety and take decision on dose escalation in Part A and on initiation of Part B and C.
 |

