The medium dose of niclosamide has been added to have the possibility to stop dosing in the 1600 mg group and continue with 1200 mg dosing in case of intolerable side effects, which may occur by accumulation of the excipient PEG-400 in the gut.

Accumulation of niclosamide is not expected after multiple dosing considering the plasma concentration-time profiles observed in Part A of the study.

Niclosamide solution will be administered once daily under fed conditions.

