## **6.2. Method of Assigning Subjects to Treatment Groups**

After written informed consent, subjects meeting all in-/exclusion criteria will be randomized at baseline (Day -1) to one of the different treatment arms:

Randomization numbers will be assigned in ascending, sequential order to eligible patients. The investigator will document the randomization number in the source data sheet and the eCRF.

The randomization list will be kept in safe and confidential custody at the CRO. Only personnel not involved in the study will have access to the list. If one of the single verum cohorts will be stopped for safety reasons, the study will nevertheless be continued with the other study drug. The use of the randomization list will then be adapted in a way that only the randomization numbers of the remaining drug will be used.

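### The Part C rule for stopping 1600 mg is inconsistent on its trigger, on which randomisation numbers continue, and on what replacements receive

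*Protocol*

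**What the plan says.** Part C randomises 12 subjects to 1200 mg, 1600 mg or placebo, four per group, for seven days. Of these groups the synopsis says: "This part consists of three treatment groups, which will start in parallel". The provisions for a stop of 1600 mg are spread over several sections.

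- **Synopsis, Part C:** "The 1600 mg niclosamide dose will be stopped and continued with the 1200 mg dose if the 1600 mg dose causes intolerable side effect". GI effects are named only as the most likely kind.
- **Section 1.3:** the 1200 mg group was added to make it possible "to stop dosing in the 1600 mg group and continue with 1200 mg dosing in case of intolerable side effects".
- **Section 3.1, Part C:** "The high dose of niclosamide solution can be stopped and continue with the medium dose in the subsequent subjects", the condition being moderate to severe GI effects.
- **Section 3.4:** the high dose "may be discontinued if moderate to severe GI side effects occur" that are attributed to PEG-400. Then "Subsequent subjects in the high dose group will receive the medium dose of 1200 mg", provided the SMC and the investigator agree.
- **Section 6.2:** if a verum cohort is stopped for safety, the study goes on and "only the randomization numbers of the remaining drug will be used".
- **Section 3.1.1:** "Replacements will receive the same treatments as the drop outs". No exception is made for a dose that has been stopped.
- **Section 4.4:** a subject with an adverse event of CTCAE Grade 3 or above must be withdrawn.

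Table 4 in section 7.2.1 equates moderate with Grade 2. Section 8.1 rests the size of Part C on eight subjects on verum. Section 8.2 analyses subjects by the treatment they received. Section 3.6 directs the SMC to section 3.4 when it decides.

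**The concern.** This is a safety rule in healthy volunteers, and the protocol expects that it may be needed. Site, SMC and the holder of the randomisation list could each follow a section of the protocol and still reach different results. They could differ on whether an event calls for a stop, whether the remaining 1600 mg places are filled at 1200 mg or left empty, and what a replacement is given. The number of actively treated subjects, and the size of the 1200 mg group on which the multiple-dose safety and PK summaries rest, would then depend on which section was read.

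**Working it through.** **Stated size.** Part C: 4 + 4 + 4 = 12, of whom 4 + 4 = 8 are on verum. Whole study: 3 × 4 (Part A) + 4 (Part B) + 12 (Part C) = 28. These match the synopsis and sections 4.1 and 8.1. No hypothesis test is planned, so there is no power figure to reproduce.

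**Trigger and force.**

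| Section | Threshold | Force | Number of subjects |
|---|---|---|---|
| Synopsis | intolerable effect, any type | mandatory | not given |
| 1.3 | intolerable effects | a possibility | not given |
| 3.1 | moderate to severe GI effects | optional | not given |
| 3.4 | moderate to severe GI effects | optional | not given |

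A Grade 2 GI event meets the threshold in 3.1 and 3.4 but is not clearly intolerable. An intolerable effect obliges a stop under the synopsis but only permits one under 3.4. By contrast, the Part A rules in section 3.3 state grades and counts.

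**Sample after a stop.** Let k be the number of subjects dosed at 1600 mg when the dose is stopped. Assume that those k keep their data, that the 1200 mg and placebo groups fill to four each, and that there are no drop-outs.

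- Section 3.4: the other 4 − k places are filled at 1200 mg. Verum = k + (4 + 4 − k) = 8; total = 8 + 4 = 12.
- Section 6.2: the unused 1600 mg numbers are skipped. Verum = 4 + k; total = 8 + k if placebo numbers continue.

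| k | 3.4: 1600/1200/placebo | Verum | Total | 6.2: 1600/1200/placebo | Verum | Total |
|---|---|---|---|---|---|---|
| 1 | 1/7/4 | 8 | 12 | 1/4/4 | 5 | 9 |
| 2 | 2/6/4 | 8 | 12 | 2/4/4 | 6 | 10 |
| 3 | 3/5/4 | 8 | 12 | 3/4/4 | 7 | 11 |
| 4 | 4/4/4 | 8 | 12 | 4/4/4 | 8 | 12 |

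Under 6.2 the eight verum subjects of section 8.1 are missed for every k below 4. As an illustration at k = 2: with no events at 1200 mg, the one-sided 95% upper bound on an event rate, 1 − 0.05^(1/n), is 39% with n = 6 (section 3.4) and 53% with n = 4 (section 6.2).

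**Replacements.** A Grade 3 GI event at 1600 mg meets the severe end of the section 3.4 trigger and also requires withdrawal under 4.4. The withdrawn subject is a drop-out, whose replacement receives 1600 mg under 3.1.1. That replacement is also a subsequent subject in the high dose group, who receives 1200 mg under 3.4 once the SMC and investigator agree.

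**Who continues on 1200 mg.** Sections 3.1 and 3.4 agree that it is subsequent subjects only. The synopsis and section 1.3 do not say.

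**The case against.** The best defence is that section 3.4 is the operative rule. Section 3.6 refers the SMC to it, it is more specific than 3.1.1 or 6.2, and an SMC charter, not shown here, may give detail. On that view a replacement in the high dose group is simply a subsequent subject, and 6.2 is general text whose reference to another study drug fits two doses of one drug poorly. This has some force. But the protocol sets no order of precedence, the synopsis states a mandatory stop, and Part C is the only part with more than one verum group running in parallel, so it is where the 6.2 instruction would apply.

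A second defence is that the groups start in parallel and no stagger is described. All four 1600 mg subjects may have started before any stop, and the counts then agree. That is correct at k = 4; k is unknown, and k = 1 is the widest gap. The replacement conflict remains even at k = 4.

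Several stronger readings are tempting but not supported:

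- **Dose groups become uninterpretable.** Analysis is by treatment received and purely descriptive. A subject given 1200 mg for all seven days belongs with 1200 mg.
- **Day 7 exposure mixes two doses.** This needs a switch within a subject. No section directs one; the synopsis and 1.3 merely fail to exclude it.
- **Placebo control is lost.** Section 6.2 does not mention placebo numbers. Skipping them is one reading of a silent text.
- **The rule is likely to fire.** The protocol gives no event rates, and under 3.4 the stop is optional and needs attribution to PEG-400.

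**Conclusion.** The rule is wrong as written and needs reconciling. Three conflicts stand in the current text: trigger and force (synopsis and 1.3 against 3.1 and 3.4), continuing randomisation numbers (3.4 against 6.2), and the treatment of replacements (3.1.1 with 4.4 against 3.4). The silence of the synopsis and 1.3 on who continues at 1200 mg is an ambiguity, not a contradiction.

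The size is a shortfall of 4 − k verum subjects under 6.2 relative to section 8.1: 3, 2 or 1 for k = 1, 2 or 3, and none at k = 4. This assumes that the other groups fill as planned and, for the totals, that placebo numbers continue. The trigger and replacement conflicts do not depend on k.

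**What to change.** Reconcile the Part C text of the synopsis and sections 1.3, 3.1, 3.1.1, 3.4, 4.4 and 6.2 into one rule. It should state the trigger and the number of affected subjects, whether the stop is mandatory or optional, which subjects change dose, and what a replacement receives after a stop. Which clinical rule applies is for the sponsor and the SMC.

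On the statistical side, make 6.2 agree with 3.4 on which randomisation numbers continue, and state that placebo numbers go on being issued after a stop. If the 6.2 approach is kept, restate the Part C verum count in section 8.1 as 4 + k when the dose is stopped after k subjects.

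The presentation of subjects moved to 1200 mg, and of anyone whose dose changed within the seven days, can be left to the SAP.

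The cost is protocol wording, with no additional subjects. The one drawback is a possibly smaller stated verum count.

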### **3.5. Premature Termination of the Study**

The study may be terminated at any time for any reason by the sponsor.

The progress of the clinical trial with regard to safety-relevant events will be monitored and, if necessary, the premature termination of the entire clinical trial will be initiated. The entire trial must be terminated prematurely for the following reasons:

- The sponsor or the investigator consider that the number and/or severity of adverse events justify discontinuation of the study cohort
- New information is received regarding product safety or other issues arise related to the trial that preclude its completion
- Intervention of the SMC, Competent Authority (CA) or involved Ethics Committee.
- In the event of a negative change in the risk/benefit ratio, a necessary adjustment of the maximum amount of insurance cover is not possible

The reason for such a decision will be documented in writing. The respective IEC and the applicable CA will be informed in writing as appropriate.

### **3.6. Safety Monitoring Committee (SMC)**

A SMC will monitor study progress and safety clinical data. Details of the members and procedures are described in the SMC charter.

The SMC will meet:

- Before dose escalation in Part A to decide, under consideration of the occurrence of safety issues and PK, whether treatment of the next higher dose cohort of the oral solution can be initiated. The meeting can be held if all subjects in each cohort completed their EOS visit.
- After Part A of the study to decide about the further dosing in Part B and Part C. The meeting can be held if all subjects completed their EOS visit.
- at any time if safety issues arise during the study

The SMC will have access to all safety, lab data and PK data during the study. It will decide under consideration of all safety issues and with respect to dose escalation and stopping rules as described in sections 3.3. and 3.4.

Initiation of the next higher dose in Part A and proceed with Part B and Part C can only occur after review of the following data by the SMC:

- [figure not shown]
- Safety data of all subjects in a given cohort until 48 h postdose
  - PK data of all subjects until 24 h postdose

### 3.7. Study Completion

Study completion is defined as the date when the last subject finishes the EOS visit and any assessments have been documented and followed up by the investigator. In case of an early study termination, it will be the date of the decision to terminate the study.

## 4. Study Population

### 4.1. Number of Subjects

This study will be performed in approx. maximum 28 healthy subjects.

### 4.2. Inclusion Criteria

Each subject must satisfy all of the following criteria to be enrolled in the study:

1. Healthy male or female subjects
2. Age 18-45 years (inclusive) at the time of informed consent signature
3. Body Mass Index (BMI) between 18.0 and 30 kg/m^2, inclusive at screening.
4. Healthy based on physical examination, medical history, vital signs, clinical laboratory tests, and 12-lead ECG performed at screening. If any of the results are abnormal, the subject may be included only if the investigator judges that the abnormalities or deviations from normal are not clinically significant.
5. A resting heart rate between 50 and 90 beats per minute
6. Men must agree to use condoms (including men who have had vasectomies) even if their partner is pregnant (this is to ensure that the fetus is not exposed to the study drug through vaginal absorption) and to not donate sperm and to not plan to father a child during the study and for 3 months after receiving the last dose of study drug. Male subjects must be counselled by the investigator that they should encourage their female partner to use a highly effective method of contraception consistent with local regulations regarding the use of contraceptive methods for subjects participating in clinical studies (e.g. prescription oral contraceptives, contraceptive injections, intrauterine device [IUD]) in addition to the condom used by the male study subject.
7. A female subject of childbearing potential must either commit to true abstinence from heterosexual contact or agree to use, and be able to comply with effective contraceptive methods with a failure rate < 1 % e.g. use of oral (estrogen and progesterone), injected or implanted hormonal methods of contraception by woman with correct and consistent use or placement of an IUD or intrauterine system (IUS) or other forms of hormonal contraception that have comparable efficacy from the time of signing the ICF and for 3 months after receiving the last dose of study drug. In addition to hormonal contraception method by woman, the male sexual partner should use a barrier method (e.g. condom).
8. Woman are considered post-menopausal and not of childbearing potential if they have had:
  - Female sterilization (have had surgical bilateral oophorectomy with or without hysterectomy), total hysterectomy or tubal ligation at least six weeks before taking

study treatment. In case of oophorectomy alone, only when the reproductive status of the woman has been confirmed by follow up hormone level assessment.

- 12 months of natural (spontaneous) amenorrhea with an appropriate clinical profile (e.g., age appropriate, history of vasomotor symptoms), confirmed by hormone level assessment.
9. Subject must have signed the informed consent form prior to the first study-related procedure indicating they understand the purpose of and procedures required for the study and are willing to participate in it.

### **4.3. Exclusion Criteria**

- 1 Known or suspected hypersensitivity to trial product or related products
- 2 Female who is pregnant, breast-feeding or intends to become pregnant or is of child-bearing potential and not using a highly effective contraceptive method.
- 3 Any disorder which in the investigator's opinion might jeopardize subject's safety, evaluation of results, or compliance with the protocol.
- 4 Aspartate aminotransferase (AST) and alanine aminotransferase (ALT) exceeding the upper limit of normal (ULN) of the clinical laboratory's reference range at screening.
- 5 Total bilirubin 20% above ULN at screening (except in case of Gilbert's disease).
- 6 Serum creatinine exceeding the ULN and/or creatinine clearance  $\leq 80$  mL/min according to MDRD equation at screening.
- 7 Serum potassium  $> 5.5$  mmol/L,
- 8 Platelets  $< 150,000$ /ml at screening.
- 9 Subject has a hepatitis B and/or C infection or human immunodeficiency virus (HIV) type-1 or HIV-2 antibodies or infection at screening.
- 10 Positive SARS-CoV-2 test
- 11 Subject has evidence of SARS-CoV-2 infection and/or subject is deemed at risk for the coronavirus disease (COVID-19) in the opinion of the treating physician or the subject has participated in another clinical study involving treatment(s), which may increase such risk.
- 12 Positive drug screen
- 13 Use of other investigational drugs at the time of enrollment, or within 5 half-lives of enrollment, or within 30 days, whichever is longer; or longer if required by local regulations.
- 14 Donated blood or blood products (approximately 450 mL) or lost a significant amount of blood within 2 months before the first administration of study drug.
- 15 Inability or unwillingness to comply with study procedures, including study prohibitions and restrictions.
- 16 Any condition for which, in the opinion of the investigator, participation would not be in the best interest of the subject (e.g. compromise the well-being) or that could prevent, limit, or confound the protocol-specified assessments
- 17 Staff member or relative of a staff member, or a subordinate relationship with the Investigator.
- 18 Vulnerable subject who lives in an institution on court or authority order.

[figure not shown]

